### DiGEM Objectives

#### Primary objective

Our primary objective is to determine whether HbA1c is significantly lower in patients with type 2 diabetes allocated to each of two intervention groups (both receiving training in the techniques of blood glucose self-monitoring, but with one additionally receiving training in the interpretation and application of the results to diet, physical activity and medication adherence) compared to patients allocated to a control group (receiving standardised usual care involving intermittent measurement of HbA1c by health professionals).

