#### Statistical aspects

In the absence of data relating to change in HbA1c we have calculated sample size conservatively based on the absolute level of HbA1c at follow up. We set out to detect a difference in HbA1c of 0.5% between any two groups. At the outset we estimated the SD of HbA1c as 1.5, based on data from the UKPDS. In practice, the SD of baseline HbA1c among the 245 patients recruited in Oxford was 0.9, but we assumed that the SD among additional patients recruited elsewhere could be as high as 1.5. With 205 further patients, the overall SD would be 1.2, and there would be 150 patients in each group (135 allowing for 10% attrition). These numbers would give 93% power to detect a difference of 0.5% in HbA1c between any two trial groups (2-tailed alpha = 0.05). Figure 1 gives estimates of likely numbers in each group and attrition.

We propose to conduct a single analysis of main trial endpoints at the end of the study. The proposed intention to treat analysis will compare mean levels of HbA1c at follow up between the three study groups, with baseline HbA1c as a covariate, using analysis of covariance. Post-hoc t-tests between groups will be conducted in the event of a statistically significant result. Subsequent analysis will include comparing the two intervention groups against the control group.

We will estimate the intervention effect in sub-groups defined by duration of diabetes (above or below median duration), current management (oral hypoglycaemic dugs or dietary management only), health status at baseline (above or below median EQ-5D score) and co-morbidity (presence or absence of diabetes related complications). We will also explore the extent to which the measures of beliefs included in the study can explain changes in behaviour; firstly by comparing mean levels of beliefs e.g. about controllability of diabetes between experimental groups and secondly by a more formal mediation analysis [28]. Within group analyses will be used to determine fidelity to protocol and conformity to the theoretical model, between group analyses will be used to assess impact of the intervention on key variables proposed by the theoretical model. Additional exploratory analysis will include changes in behaviour in relation to perceived threat and changes in perceived thereat from diabetes.

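### The primary objective is each intervention arm versus control, but the plan reaches those contrasts only after a three-group test or as follow-on analysis with no fixed rule, and the stated 93% power is not that of the planned sequence

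*Protocol article*

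**What the plan says.** The Primary objective section sets out to "determine whether HbA1c is significantly lower in patients with type 2 diabetes allocated to each of two intervention groups" than in control. That is two contrasts: self-testing versus control and self-monitoring versus control.

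Statistical aspects plans the analysis in three sentences:

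- The main comparison, by intention to treat, is to "compare mean levels of HbA1c at follow up between the three study groups, with baseline HbA1c as a covariate, using analysis of covariance".
- Pairwise testing depends on the outcome of that comparison: "Post-hoc t-tests between groups will be conducted in the event of a statistically significant result".
- The comparison with control comes last: "Subsequent analysis will include comparing the two intervention groups against the control group".

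The sample size in the same section targets a pairwise difference: "We set out to detect a difference in HbA1c of 0.5% between any two groups". With an overall SD of 1.2 and 135 patients per group after attrition, it concludes: "These numbers would give 93% power to detect a difference of 0.5% in HbA1c between any two trial groups", at a two-sided 5% level.

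**The concern.** The question the trial was set up to answer is not the one its main test addresses. A three-group test asks whether any of the three means differ. The control contrasts then appear either among post-hoc t-tests, next to an intervention-versus-intervention comparison that is not in the primary objective, or as follow-on analysis.

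The third sentence is open in two ways. It does not say whether the control comparison depends on a significant three-group test. It can also mean each arm against control, or both arms pooled against control.

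A non-significant three-group test alongside a nominally significant control contrast is a foreseeable result. On the present wording, one reader could say the primary objective was not met and another that it was. The power figure is also quoted for a single two-group comparison, which is not the sequence planned.

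**Working it through.** **Inputs, all from Statistical aspects:** 135 analysed per group, SD 1.2, true difference 0.5% HbA1c, two-sided 5%. The sample size was set on the follow-up level, so no gain from the baseline covariate is taken. The position of the third arm is not given and is varied below.

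**1. The plan's own figure.** The standard error of a two-group difference is 1.2 × √(2/135) = 0.146. The noncentrality is 0.5/0.146 = 3.42, and power at two-sided 5% is 92.7%. The stated 93% is correct for one stand-alone two-group t-test.

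**2. The three-group test.** With three groups the error degrees of freedom are 3 × 135 − 3 = 402, and the 5% critical value of F(2, 402) is 3.02. The noncentrality is λ = n Σ(μᵢ − μ̄)²/σ².

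- Self-testing midway (effects 0, 0.25, 0.5): λ = 135 × 0.125/1.44 = 11.7, power 87.3%.
- Self-testing equal to control (0, 0, 0.5): λ = 135 × 0.1667/1.44 = 15.6, power 95.1%.

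When the third observed mean lies exactly midway, F = t²/2 for the outer contrast. That contrast then needs |t| above √(2 × 3.02) = 2.46 to pass the gate, against 1.97 on its own.

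**3. The sequences, simulated** (1,000,000 trials each, pooled variance on 402 df). Entries are the power for the self-monitoring versus control contrast.

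| Self-testing effect | Ungated t-test | Gated by the three-group test | Step-down Dunnett |
|---|---|---|---|
| Equal to control | 92.7% | 91.2% | 88.7% |
| Midway | 92.7% | 86.8% | 88.9% |
| Equal to self-monitoring | 92.7% | 91.2% | 91.6% |

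In the midway case the contrast is significant but blocked by the three-group test in about 6% of trials. At SD 1.5, the plan's first assumption, this is about 11%.

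**4. Chance of at least one false claim versus control when no arm differs.**

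- Both control contrasts gated: 4.2%.
- Both run regardless of the gate, 5% each: 9.0%.
- Step-down Dunnett: 5.0%.

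**5. The pooled reading.** If only self-monitoring works, the pooled difference is 0.25, with standard error 1.2 × √(1.5/135) = 0.126. The noncentrality is 1.98 and power about 50%. If the pooled comparison is run regardless of the gate, the chance that it or the three-group test is falsely significant is 7.5%. A pooled result also cannot speak to each arm.

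**The case against.** **Error control.** A reader might infer that the control contrasts have no sound error control. The article does not support that. With exactly three groups, a 5% three-group test followed by 5% t-tests is Fisher's protected procedure, which holds familywise error at 5% in the strong sense. Step 4 agrees under the global null. When one arm truly differs by 0.5%, the null arm's contrast is falsely significant in 5.0% of trials. The 9% arises only if the follow-on comparison ignores the gate, and the sentence, coming directly after the gating rule, does not say so.

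**Alternatives, not a sum.** The gated reading loses power and keeps the error rate. The ungated reading does the reverse. The two harms cannot both be charged to the plan.

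**Size of the power loss.** It is small, and 87% needs self-testing to lie midway. The planned baseline adjustment is ignored throughout. The article gives no baseline-to-follow-up correlation. If one assumes 0.3, 0.4, 0.45 or 0.5, gated power in the midway case becomes about 90%, 92%, 94% or 95%. A correlation of about 0.45 therefore recovers the stated figure.

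**Detail left elsewhere.** A statistical analysis plan not shown here may settle the multiplicity rule. That covers the missing detail. It does not cover the mismatch, because the article itself states the objective, the three-group test, the gate and the power.

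These points stand and limit the finding. The objective and the main test still differ, and 93% is still the power of another procedure.

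**Conclusion.** The point holds as a should-fix. The primary objective names two control contrasts. The analysis section makes a three-group test the main analysis and leaves open the gate and the form of the control comparison.

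At 135 per group and SD 1.2, with no covariate gain, the gated sequence has 87% to 91% power for a true 0.5% control contrast, against the 93% stated. The lower end assumes self-testing midway between the other arms. Running both contrasts regardless keeps 93% power but gives a familywise error of about 9%. None of the error-controlled procedures worked through here reaches 93% on the plan's own assumptions.

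A reader might also infer that the trial is underpowered. These figures do not show that: even the lowest at SD 1.2 is above the 80% in the Abstract, and baseline adjustment can only help.

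**What to change.** In Statistical aspects:

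1. Name the two baseline-adjusted ANCOVA contrasts, self-testing versus control and self-monitoring versus control, as the primary analysis, with no three-group test as a gate.
2. State one 5% familywise rule for the pair. Step-down Dunnett is one suitable choice (critical |t| about 2.22 for the larger contrast, then 1.97). Other valid rules exist.
3. Make self-monitoring versus self-testing a secondary comparison, and say that any pooled comparison with control is supportive only.
4. Restate power for that rule: about 89% at SD 1.2 before any covariate gain.

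The cost is wording only. A single analysis is planned at the end of the study, so the rule can be fixed beforehand without touching patients or data. The stated power becomes slightly less favourable. Compared with the gated sequence, step-down Dunnett gains about 2 points in the midway case (88.9% against 86.8%) and loses about 2.5 points if self-testing equals control (88.7% against 91.2%). The main gain is that the primary question is always tested, at a known error rate.

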#### Economic evaluation

The economic evaluation will be on an intention-to-treat basis. A cost-effectiveness/cost-utility analysis will be performed in which the difference in effectiveness will be compared to the difference in total costs between each study intervention group, and the results will be expressed as incremental cost-effectiveness ratios. Effectiveness will be measured in terms of change in HbA1c, and modelled for life years gained and quality adjusted life years gained. Unit costs will be attached to the resource items collected from the healthcare resource utilisation assessment using published national average costs and tariff averages for procedures to calculate costs. Mean values and 95% confidence intervals will be reported for each component of resource use and cost and for total costs and effectiveness. Sensitivity analyses will be performed on all aspects of the economic evaluation that are subject to uncertainty.

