#### Secondary objectives

Secondary objectives are:

(i) To compare well-being, satisfaction, health service use and economic cost between allocated groups.

(ii) To conduct an exploratory analysis of changes in mean HbA1c between regimens among sub-groups defined by duration of diabetes, current management, self-reported health status and co-morbidity.

(iii) To test how self-monitoring influences beliefs and behaviour using measures chosen on the basis of theoretical models of behaviour change.

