### Baseline measures and follow up

The primary outcome measure is change in HbA1c between the baseline measurement at the assessment visit and 12-month visit. Secondary outcome measures include change in systolic and diastolic blood pressure, weight, serum cholesterol and HDL, self-reported smoking status, dietary intake and physical activity (the Diabetes Self Care Activities Questionnaire) [22], medication adherence (The Medication Adherence Rating Scale) [23], and the scores in the Diabetes Treatment Satisfaction Questionnaire [24], and the Well-being Questionnaire (12 item) [25].

Beliefs about diabetes and its management are assessed using the Illness perceptions Questionnaire [26], Beliefs about Medicines Questionnaire [27], and a questionnaire developed for the study about the effectiveness of changes in eating and physical activity on the course of diabetes, and attitudes to blood glucose self-monitoring. Table 1 summarises the measures and their timing.

**Table 1 T1:** Study measures

**Measures**	**Baseline**	**3 months**	**6 months**	**9 months**	**12 months**

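### As written, QALYs are modelled from HbA1c change with no observed utility input, so the cost-utility result would not register a quality-of-life effect of self-monitoring that bypasses HbA1c

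*Protocol article*

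**What the plan says.** The economic plan is one paragraph, under Economic evaluation. It announces the type of analysis ("A cost-effectiveness/cost-utility analysis will be performed") and then fixes the effect measure: "Effectiveness will be measured in terms of change in HbA1c, and modelled for life years gained and quality adjusted life years gained". No utility instrument is named there. The paragraph ends with a general commitment: "Sensitivity analyses will be performed on all aspects of the economic evaluation that are subject to uncertainty".

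EQ-5D appears once in the article, under Statistical aspects, where one subgroup factor is "health status at baseline (above or below median EQ-5D score"). Secondary objectives gives the same factor as self-reported health status, among "sub-groups defined by duration of diabetes, current management, self-reported health status and co-morbidity".

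Baseline measures and follow up names the outcome measures and questionnaires, and adds that "Table 1 summarises the measures and their timing". EQ-5D is in neither that text nor any row of Table 1 as it could be read. Well-being and satisfaction have an objective of their own: "To compare well-being, satisfaction, health service use and economic cost between allocated groups".

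**The concern.** The strategies differ in what patients are asked to do. Under Post-randomisation, the self-testing group takes three readings on each of two days a week, about six a week, and the self-monitoring group is also asked to interpret and act on its readings. Either demand could raise or lower quality of life without moving HbA1c. The article itself treats well-being as an outcome in its own right, in Secondary objectives and in the abstract's Discussion.

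A QALY driven by HbA1c change sees none of this. If monitoring lowered quality of life while HbA1c fell slightly, the model would report a QALY gain. If it improved quality of life and left HbA1c unchanged, the model would report no gain. QALYs are the denominator of cost per QALY, so a small omitted term can shift the ratio a good deal when the modelled gain is itself small. The abstract says the trial should support, focus or discourage particular uses of self-monitoring, and cost per QALY is part of that evidence.

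Timing matters too. Utilities not collected at a visit cannot be recovered later, and the article reports that recruitment is past half.

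**Working it through.** **1. The sections side by side**

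| Place in the article | What it gives |
|---|---|
| Economic evaluation | HbA1c change, modelled to life years and QALYs; no observed utility named |
| Statistical aspects | Baseline EQ-5D, median split, for one subgroup |
| Secondary objectives | The same subgroup factor as self-reported health status; well-being and satisfaction compared separately |
| Baseline measures and follow up | Named questionnaires; EQ-5D not among them |
| Table 1, as it could be read | No EQ-5D row; also no row for the treatment satisfaction or self-care activities questionnaires, which the text does name |
| Study measures | Self-report measures completed at the assessment visit; repeat measurements at 52 weeks, with no instrument named |

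Table 1 is weak evidence on its own, since it lacks two questionnaires that the text includes. EQ-5D differs from those two in being missing from both places.

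**2. The number per arm**

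The article gives no figure for utility or QALYs, so there is none to reproduce. The 135 per arm used below comes from Statistical aspects: 450 / 3 = 150, and 150 × 0.90 = 135. The power stated with it reproduces: 0.5 / (1.2 × √(2/135)) = 3.42; 3.42 − 1.96 = 1.46; power 92.8%, against 93% stated. The sample size is not in question here.

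**3. Size of the omitted term (assumed shifts, none in the article)**

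- Immediate shift lasting 12 months: QALY = u × 1, so 0.01 to 0.05 gives 0.01 to 0.05.
- Linear build-up over 12 months: QALY = u × 0.5, so 0.005 to 0.025.

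**4. Precision of an observed utility difference at 52 weeks**

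Assumed: SD 0.20 to 0.25, baseline correlation 0.6.

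SE = SD × √(2/n) × √(1 − 0.6²), with √(2/135) = 0.1217 and √(1 − 0.36) = 0.8.

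- SD 0.20: SE = 0.20 × 0.1217 × 0.8 = 0.0195; half-width 1.96 × 0.0195 = 0.038.
- SD 0.25: SE = 0.25 × 0.1217 × 0.8 = 0.0243; half-width 0.048.

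Without baseline adjustment, SD 0.20 to 0.30 gives half-widths of 0.048 to 0.072.

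With only two time points and straight-line interpolation, the QALY difference is half the 52-week utility difference. Its half-width is then 0.019 to 0.024, set against 0.005 to 0.025 QALY, so the ratio of effect to precision is unchanged.

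**5. If only later recruits can supply EQ-5D**

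Suppose neither time point has been collected for the 245 Oxford patients. The 205 others give 205 / 3 × 0.9 = 61.5 per arm and √(2/61.5) = 0.180. Half-widths become 1.96 × 0.20 × 0.180 × 0.8 = 0.057 and 1.96 × 0.25 × 0.180 × 0.8 = 0.071. This is a worst case, not something the article implies.

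**The case against.** The strongest reply is that this is a condensed article. One paragraph on economics cannot carry the full plan, and the source of utility values is the kind of detail a fuller document would hold. The text does not exclude observed utilities, it calls the analysis cost-utility, and it plans broad sensitivity analyses. The measures list opens with "Secondary outcome measures include change in systolic and diastolic blood pressure, weight, serum cholesterol and HDL, self-reported smoking status", and a list introduced by include need not be complete. Well-being and satisfaction are compared between groups anyway, so harm to well-being would be reported beside the economic result.

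Much of this stands. A reader might infer that QALYs come from HbA1c alone and that no other input is possible. The text does not say so; it supports only the narrower statement that HbA1c is the sole effect measure named. A reader might also infer that the health-status subgroup has no source variable and cannot be formed. The documents do not support that: Statistical aspects names baseline EQ-5D as the variable, which implies that it is collected, and the assessment visit already includes self-report questionnaires. EQ-5D may even be among the measures repeated at 52 weeks, though nothing says so.

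Three things survive. The article states positively what effectiveness is measured by, so this is more than silence. Sensitivity analyses can vary model inputs but cannot supply utilities that were not collected. And a well-being score reported separately does not enter the QALY, because nothing links the 12-item questionnaire to utility.

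**Conclusion.** The point holds for the plan as written: the QALY route runs through HbA1c change, no observed utility is named, and a direct quality-of-life effect of self-monitoring would not reach the cost-utility result. The absence of EQ-5D from the measures text and Table 1 is a minor inconsistency with Statistical aspects. It does not show that the subgroup is impossible.

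The size cannot be read from the documents. The utility shift, SD and correlation are all assumed. On those assumptions the omitted term is 0.005 to 0.05 QALY per patient over the year. A half-width of 0.04 to 0.05 on the utility scale, about the top of the assumed range of shifts, would limit larger effects but could not tell most of that range from zero. Observed EQ-5D would therefore make the uncertainty visible more than it would settle the question.

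This is a worthwhile and cheap improvement to a secondary analysis. The primary HbA1c comparison and its power are not affected.

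**What to change.** - In Baseline measures and follow up and in Table 1, list EQ-5D at baseline and at the 52-week visit. If it is not already collected at 52 weeks, add it for patients who have not yet passed that visit, and report how many contribute.
- In Economic evaluation, calculate within-trial QALYs from observed EQ-5D by arm, adjusted for baseline EQ-5D. Use HbA1c modelling for the period beyond 12 months, and keep the HbA1c-only model as a sensitivity analysis.
- If baseline EQ-5D was not in fact collected for patients already recruited, say so. Baseline adjustment and the health-status subgroup would then be confined to those who have it.

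The cost is one short questionnaire at an existing visit, a few minutes of patient time, and a change of wording. The confidence interval on QALYs will be wider than a purely modelled figure would show. With two time points only, an immediate shift would be recorded at half its size under straight-line interpolation, and the report should state this.

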## Discussion

This study will make an important contribution to the evidence-base for the use of blood glucose self-monitoring in non-insulin using patients with type 2 diabetes. It will provide a robust estimate of overall effect of use of the meters for self-testing alone and with a more intensive programme to support people in using their test results actively in self management of health related behaviours.

This trial will address two main problems associated with previous trials. Firstly, the study is adequately powered to identify a reduction in HbA1c of 0.5%, which is associated with clinically important reductions in diabetic complications. Secondly, study participants allocated to the most intensive group are explicitly supported in interpretation of their study results in relation to lifestyle changes. This is the first study in this field to use standardised delivery of these interventions together with the other measures supporting fidelity to protocol.

A further strength of the trial design is the inclusion of measures that explore the extent to which the interventions being used influences beliefs and behaviour. It will be possible to test whether the interventions, especially that based on the CSM, are successful in altering beliefs about diabetes, and whether the interventions were delivered with fidelity to their theoretical basis. It will also be possible to test whether differences in behaviour and HbA1c between experimental groups are due to the interventions bringing about changes in beliefs, as proposed by the CSM. Depending on the pattern of findings from the mediation analysis, it will be possible to conclude there is no mediation (none of the causal effect of intervention on behaviour is transmitted by beliefs about diabetes), total mediation (all of the effect is transmitted by beliefs) or partial mediation (part of the effect is transmitted by beliefs and part is direct). This will provide information about the extent to which the CSM can usefully inform intervention content to change beliefs and behaviours.

The trial is mainly generalisable to that group of patients willing to be randomised to no self-testing. It will be limited in its ability to inform management of people who are enthusiastic about regular meter use. Not only does this group include people who have already been recommended to use a meter by their doctor or nurse, but also includes people who have obtained a meter in the absence of medical advice. In health service terms, these are people who are likely to obtain a meter whether or not they are prescribed or offered one. A trial to address management in this group would be more difficult because of difficulties in identifying individuals who are both enthusiasts, yet willing not to be exposed to the use of self-monitoring. However, the detailed information about beliefs and the pre-specified sub-group analyses will provide information to inform design of future studies in this area by allowing refinement of interventions and accurate estimates to inform sample size calculations The detailed information from blood glucose diaries and relation to outcomes will also inform the refinement of training programmes and data interpretation.

This trial has features of both a pragmatic and an explanatory trial [29]. The use of three parallel groups, delivery of interventions according to protocol and extensive measures along a causal pathway are characteristic of phase III or explanatory trials. The use of a primary care setting, comparison of three feasible health service strategies, wide range of recruitment a long duration, and estimation of costs are, however, more characteristic of a pragmatic trial. This hybrid design, whilst answering a health service question, will provide additional information to guide future research. The extent to which the trial is able to deliver data that informs both of these agendas will inform design of trials of emerging health technologies where the opportunity to understand underlying mechanisms may be lost in an effort to simplify protocol design.

The results of this trial will be available in 2007.

